### Measures and Outcomes

Sociodemographic characteristics of study participants, such as age, migration background, marital status, and socioeconomic status (including education, employment status, occupation, and income), as well as history of chronic disease and current diagnoses are assessed during the telephone interview.

### Primary Outcome

The primary outcome is the number of steps assessed via pedometers. Participants are asked to track their steps using the YAMAX EX210 pedometer, which records the daily number of steps. They are also requested to complete a wear-time diary to document the steps walked every day, the times the pedometer is worn, and the possible reasons for not wearing it. PA is also assessed using the Global Physical Activity Questionnaire in the telephone-administered questionnaire [32]. It is one of the most frequently used questionnaires for measuring PA with high levels of reliability and validity reported when comparing it with other PA questionnaires (International Physical Activity Questionnaire—Short Form and European Health Interview Survey—Physical Activity Questionnaire) [33]. On the basis of the Global Physical Activity Questionnaire, the number of minutes spent on MVPA and different types of movement will be determined (eg, for transport, see Table 1). This questionnaire was chosen because it is also used in the National Cohort (NAKO) health study [34], a large German national cohort, allowing for a comparison of PA levels of our sample to a large population-based sample.

Furthermore, a subsample of our study participants also receives an accelerometer (wCT3X-BT) to track habitual PA. Participants are instructed to position the device at their nondominant wrist during the day to capture triaxial acceleration at a sample rate of 30 Hz. Data will be processed with ActiLife (version 6.13.4) software (ActiGraph LLC), using the algorithm by Choi et al [38] to derive valid wear times with at least 4 days of a minimum 8 hours (480 minutes) wear time. Within 10-second epochs, data are analyzed using cut-off points for MVPA, energy expenditure, and metabolic equivalent of tasks, according to Freedson et al [39].

**Table 1 table1:** Outcomes assessed in the telephone-administered interviews (part 1).

Instrument or scale and outcome				Time of assessment
**Socioeconomic characteristics**				
	**NAKO^a^ core interview [34]**			
		Date of birth	T_0_^b^	
		Country of birth	T_0_	
		Country of birth outside of Germany	T_0_	
		Time since living in the territory of the Federal Republic of Germany or DDR	T_0_	
		Nationality (German vs other)	T_0_	
		Country of birth (father and mother)	T_0_	
		Marital status	T_0_	
		In a relationship	T_0_	
		Living together with partner	T_0_	
		Living district	T_0_	
		Type of residence	T_0_	
		Number of individuals living in the household	T_0_	
		Number of individuals in the household >14 years	T_0_	
		Highest education degree obtained	T_0_	
		Types of educational qualifications	T_0_	
		Other types of educational qualifications	T_0_	
		Employment status (eg, full time or part time or unemployed)	T_0_	
		Working hours per week	T_0_	
		Previous employment status (full time or part time)	T_0_	
		Occupation	T_0_	
		Income level	T_0_	
		Average net monthly income	T_0_	
	**NAKO “Corona-questionnaire” CO-1 question no. 19 [35]**			
		Changes at work due to the COVID-19 pandemic	T_0_, T_1_^c^	
	**Self-generated item**			
		City that participant is working in	T_0_	
	**ALPHA^d^ long version** **[36]**			
		Distance to work (km)	T_0_	
	**Züll [37]**			
		Type of occupational group	T_0_	
		Self-employed or employed	T_0_	
**Built environment and PA^e^**				
	**ALPHA environmental questionnaire (long version) [36]**			
		Type of resident buildings in the immediate neighborhood	T_0_	
		Pedestrian accessibility of stores in the immediate neighborhood	T_0_	
		Infrastructure of footpaths and cycle tracks in the immediate neighborhood	T_0_	
		Quality of the living environment in the immediate neighborhood	T_0_	
		Safety in the living environment in the immediate neighborhood	T_0_	
		Attractiveness of the living environment in the immediate neighborhood	T_0_	
		Connectivity of the living environment in the immediate neighborhood	T_0_	
		Private equipment to support PA	T_0_	
		Equipment in the work environment	T_0_	
**PA**				
	**GPAQ^f^** **[32]**			
		Intensive PA during paid and unpaid work	T_0_, T_1_	
		Days of intensive PA in a usual week at work	T_0_, T_1_	
		Time of intensive PA on such a day at work	T_0_, T_1_	
		Moderate PA at work	T_0_, T_1_	
		Days of moderate PA in a usual week at work	T_0_, T_1_	
		Time of moderate PA on such a day at work	T_0_, T_1_	
		Locomotion by foot or bicycle	T_0_, T_1_	
		Days in a usual week getting around from one place to another by foot or bicycle	T_0_, T_1_	
		Time invests to get from one place to another by foot or bike	T_0_, T_1_	
		Intensive PA during leisure time	T_0_, T_1_	
		Days of intensive PA in a usual week during leisure time	T_0_, T_1_	
		Time of intensive PA in a usual week during leisure time	T_0_, T_1_	
		Moderate PA during leisure time	T_0_, T_1_	
		Days of moderate PA in a usual week during leisure time	T_0_, T_1_	
		Time of moderate PA in a usual week during leisure time	T_0_, T_1_	
		Time of sedentary behavior on a usual day	T_0_, T_1_	
		Changes of PA in the past year in general	T_0_, T_1_	
	**NAKO “Corona-Questionnaire” CO-1 question number 31 [35]**			
		Changes of PA caused by the COVID-19 pandemic	T_0_, T_1_	

^a^NAKO: National Cohort Health Study.

^b^Baseline assessment.

^c^Follow-up assessment.

^d^ALPHA: Instruments for Assessing Levels of Physical Activity and Fitness

^e^PA: physical activity.

^f^GPAQ: Global Physical Activity Questionnaire

### Secondary Outcomes

Secondary outcomes assessed at baseline and follow-up in the telephone-administered interview are described in detail in Table 2.

Briefly, at the individual level, height and weight, general self-rated health, and health behavior (smoking status, fruits and vegetables consumption, and alcohol use) are assessed. In addition, the determinants of PA are assessed (eg, social support). At the environmental level, perceptions of characteristics of the physical environment relevant for engaging in PA are assessed. To assess knowledge and awareness of intervention messages and activities spread and implemented in the intervention city districts, self-generated items are included in the follow-up questionnaire. Study participants are also asked about health care use (physician’s visits, contacts with therapists, hospital stays, and rehabilitation) retrospectively for the previous 6 months and costs pertaining to devices bought to support engagement in PA or membership fees (eg, gym membership), as well as sick leave days.

**Table 2 table2:** Outcomes assessed in the telephone-administered interviews (part 2).

Instrument or scale and outcome				Time of assessment
**Determinants of PA^a^**				
	**GEDA^b^ [40], question no. 104 and 105 + 1 self-generated item**			
		Reasons to be or not to be physically active (including pandemic)	T_0_^c^, T_1_^d^	
	**GEDA [40], question no. 102**			
		Intention to increase PA in future	T_0_, T_1_	
	**Sudeck et al** **[41]**			
		Movement-related self-efficacy	T_0_, T_1_	
	**Self-generated items**			
		General knowledge of health benefits of PA, tracking of PA to date (use of devices; eg, pedometer, wearable, or smart watch)	T_0_, T_1_	
	**Intention to be physically active [21]**			
		How would you like to be physically active more often in the future?	T_0_, T_1_	
	**Modified version of questionnaire of Chernyak et al [42]**			
		Purchases of equipment to promote your fitness, health and well-being (past 6 months)	T_0_, T_1_	
**Health status**				
	**SF-1^e^ [43]**			
		How would you describe your health in general?	T_0_, T_1_	
	**EQ-5D-5L [44]**			
		Perceived health (eg, mobility, pain or physical discomfort, or anxiety)	T_0_, T_1_	
	**GEDA [45]**			
		Do you have a chronic illness or long-term health problem? (>6 months)	T_0_	
		Present diseases or conditions in the past 12 months	T_0_	
		Have you had high blood pressure or hypertension in the last 12 months?	T_0_	
		Have you ever been diagnosed with high blood pressure by a physician?	T_0_	
		Are you currently taking antihypertensive medications?	T_0_	
		Have you had elevated blood lipids or elevated cholesterol in the past 12 months?	T_0_	
		Have you ever been diagnosed with elevated blood lipids or elevated cholesterol by a physician?	T_0_	
		Are you currently taking medication for elevated cholesterol?	T_0_	
		Smoking habits	T_0_, T_1_	
	**GEDA [45], modified**			
		How often do you eat fruits, vegetables and salad?	T_0_, T_1_	
		How many servings of fruits, vegetables and salad do you eat per day?	T_0_, T_1_	
	**SOEP^f^-Core–2018, question no. 146 [46]**			
		What is your height in cm?	T_0_, T_1_	
	**SOEP-Core–2018, question no. 147 [46]**			
		How many kilograms do you currently weight?	T_0_, T_1_	
	**Alcohol Use Disorders Identification Test Short Version, translation from PROMOTE I [27,47]**			
		How often do you drink alcohol?	T_0_, T_1_	
		If you drink alcohol in a day, how many alcoholic beverages do you typically drink?	T_0_, T_1_	
	**Modified version of the questionnaire of Chernyak et al [42]**			
		Have you seen a physician in the last 6 months?	T_0_, T_1_	
		Which physicians have you seen in the last 6 months? (eg, general practitioner, gastroenterologist, diabetologist)	T_0_, T_1_	
		How many contacts you had in each of the last 6 months and how much time you spent in total on your outpatient?	T_0_, T_1_	
		Have you been to a therapist (eg, psychotherapist, physical therapist, speech therapist) for treatment in the last 6 months?	T_0_, T_1_	
		Which therapists have you seen in the last 6 months?	T_0_, T_1_	
		How many treatment sessions have you had in each of the last 6 months? And what is the total amount of time you spent on your treatment sessions?	T_0_, T_1_	
		Have you been hospitalized for inpatient treatment in the last 6 months?	T_0_, T_1_	
		Please indicate the reason and duration of stay for each hospitalization.	T_0_, T_1_	
		Have you been to rehabilitation in the last 6 months?	T_0_, T_1_	
		Indicate for each stay whether it was outpatient or inpatient rehabilitation. Please indicate the duration of your stay.	T_0_, T_1_	
		Please indicate how many days in total.	T_0_, T_1_	
		If your sick leave has been for more than 6 months, please indicate how many days you have been on sick leave.	T_0_, T_1_	
**Competences**				
	**German translation of ICECAP-A^g^ [48]**			
		Feeling safe and secure	T_0_, T_1_	
		Love, friendship, and support	T_0_, T_1_	
		Be independent	T_0_, T_1_	
		Performance and progress	T_0_, T_1_	
		Pleasure and enjoyment	T_0_, T_1_	
**Movement-related networks and social networks**				
	**Jackson et al [49]; Fuchs [50], adapted**			
		Perceived social support for PA by family members and friends	T_0_, T_1_	
**Perception and use of the intervention^h^**				
	**Self-generated items**			
		Awareness of the intervention, use of various intervention components	T_1_	

^a^PA: physical activity.

^b^GEDA: Gesundheit in Deutschland aktuell.

^c^Baseline assessment.

^d^Follow-up assessment.

^e^SF-1: Short Form-1.

^f^SOEP: Sozio-oekonomisches Panel.

^g^ICECAP-A: The ICEpop CAPability measure for adults.

^h^Only assessed in the intervention group.

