Is the intervention “10,000 Steps Ghent” adaptable and transferrable to the context of city districts in the state of North Rhine-Westphalia?Is the intervention “10,000 Steps Duesseldorf” effective for the promotion of PA among residents of the districts involved?Do individuals located in the city that the intervention is implemented in (Duesseldorf) engage in more PA compared with individuals located in the control city (Wuppertal) after 1 year? Does the absolute number of steps taken per week increase more for individuals residing in the intervention city than in the control city?Does the proportion of those achieving the PA goal of 10,000 steps increase more in the intervention than in the control city after 1 year of potentially being able to participate in intervention activities?To what extent can these differences be attributed to the adoption, implementation, and maintenance of the intervention in the intervention city compared with the control city?What are the costs associated with the provision of the intervention? Does the intervention affect health care use and indirect costs? Is the intervention cost-effective in terms of additional costs per additional person who achieves the PA goal of 10,000 steps and additional costs per additional quality-adjusted life year (QALY) gained compared between the intervention and control cities after 1 year of potentially being able to participate in intervention activities?

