The baseline assessments started at the end of May 2021 and were completed at the end of March 2022. Baseline assessment entails a questionnaire completed by participants over the phone. Two study nurses and 4 student assistants underwent structured training to conduct the 1-hour telephone interviews. Data entry is done simultaneously to the interview over the secured web application, REDCap (Research Electronic Data Capture; Vanderbilt University). The respective REDCap study database is hosted at the Institute for Biometrics and Epidemiology at the German Diabetes Center Duesseldorf and is part of the regular Institute for Biometrics and Epidemiology at the German Diabetes Center IT environment with respect to data security and backups. After the interview, study participants are asked to track their PA over 7 consecutive days using the YAMAX EX210 pedometer, which records daily number of steps. In addition, they are asked to complete a wear-time diary to document the steps walked every day, the times the pedometer was worn, and the possible reasons for not wearing it. After 7 days, participants return the pedometer to the study team via mail, using a stamped return envelope provided by the study team. To validate the pedometer data, a subsample of approximately 30% of study participants receives an accelerometer (ActiGraph wCT3X-BT; ActiGraph LLC) in addition to the pedometer, which they are asked to return in a stamped return envelope after 7 days of wear time. The intervention is being implemented in Duesseldorf for 1 year since April 2022, and follow-up assessments will be conducted, starting in May 2023. The same participants who participated in the baseline assessments will be contacted again via mail, invited to participate in the telephone-based interviews again, and asked to wear pedometers (and accelerometers) for 1 week afterward. To ensure confidentiality, all person-related data assessed in this study will be pseudonymized; that is, all study participants will be assigned an ID number. The roster with the names and ID numbers will be saved in a password-protected file on the server of the Institute of Medical Sociology. The data will be stored for 10 years after the completion of the trial and deleted afterward.

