To estimate reach, first, the number of organizations potentially participating in the program in each intervention district will be determined based on the commercial register or by the Chamber of Commerce and Industry. Second, the number of organizations participating in the program will be assessed and surveyed using the web-based questionnaire. Furthermore, the proportion of individuals who were aware of intervention activities will be calculated, and to determine representativeness, age, gender, level of education, and occupation of those aware of the intervention will be compared with those unaware of the intervention. Effectiveness will be determined by comparing the 4 domains of active living (PA for transport, to work, in the household, and during leisure time activities) among individuals with and without awareness of the intervention. Adoption will be determined by estimating the proportion and representativeness of organizations implementing the intervention (compared with those not implementing the intervention). The implementation of the different intervention components (website, print-based materials, and initiation of partnerships) will be assessed, and an implementation score ranging from 0 to 100 will be calculated (see the study by Van Acker et al [51] for more details regarding the calculation of the score). To estimate maintenance, the proportion of organizations that voiced the intention to maintain the intervention will be determined.

Example items of the web-based questionnaire used in the process evaluation.

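### Only Duesseldorf participants get the campaign awareness and use items, and they get them before the pedometer week: a possible one-sided prompt, with no direct measure of campaign exposure in Wuppertal

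*Protocol article*

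**What the plan says.** Four places in the protocol article bear on this.

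- **Table 2, last block (perception and use of the intervention).** The entry is "Awareness of the intervention, use of various intervention components", assessed at T1 only, with the footnote "Only assessed in the intervention group".
- **Secondary Outcomes.** For knowledge and awareness of campaign messages and activities, "self-generated items are included in the follow-up questionnaire".
- **Recruitment.** At baseline the order is interview, then wear: "After the interview, study participants are asked to track their PA over 7 consecutive days". Follow-up keeps that order: baseline participants are "invited to participate in the telephone-based interviews again, and asked to wear pedometers (and accelerometers) for 1 week afterward".
- **Primary Outcome.** "The primary outcome is the number of steps assessed via pedometers". Participants also enter each day's count in a diary, so they see their own steps.

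No item in Table 1 or Table 2 asks Wuppertal participants about the campaign. The nearest item given to both arms is the city in which the participant works (Table 1), asked at T0 only, before the intervention started.

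**The concern.** The intervention carries a step target in its name, and the primary outcome is a week of self-observed step counts. Asking one arm, before that week, whether they know the campaign and which parts they used reminds that arm of the target. The other arm gets no such reminder. If the reminder changes walking during the wear week, the between-city contrast picks up a measurement effect that is not an effect of the intervention.

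The planned safeguards would not remove it. The items are absent at T0, so adjustment for baseline cannot capture it. Propensity weighting balances covariates, not the measurement procedure at T1. Blinded analysis comes after the data have been collected.

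A second gap follows from the same footnote. The campaign uses a website, mass media and social media, which could reach Wuppertal residents. Without control answers the trial cannot say how many controls were exposed. It also cannot say how many people claim to know a campaign they never met, so the awareness proportion planned under Process Evaluation has no reference level.

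**Working it through.** **Step 1: the order of events at T1, by city.**

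| | Duesseldorf | Wuppertal |
|---|---|---|
| Physical activity questionnaire, intention, self-efficacy, knowledge, tracking devices | yes | yes |
| Campaign awareness and use items | yes | no |
| Then: pedometer week with daily diary (primary outcome) | yes | yes |

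The arms differ in one row, and that row comes before the outcome. The length of the gap between interview and wear week is not stated, nor is the place of the items within the interview.

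**Step 2: the plan's own figure.** Inputs from Sample Size Calculation: difference 1000 steps, SD 4500 (stated as an upper bound), two-sided 5%, power 80%. The noncentral t calculation gives 318.84, rounded up to 319 per arm, or 638 in total. This matches the stated 638.

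**Step 3: standard error at that size.** SE = 4500 × √(2/319) = 356 steps.

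**Step 4: differential prompt, no true effect (assumed sizes).** With bias b, the two-sided rejection rate is 1 − Φ(1.96 − b/SE) + Φ(−1.96 − b/SE).

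| Assumed b (steps) | Share of 1000 | Rejection rate |
|---|---|---|
| 0 | 0% | 5.0% |
| 100 | 10% | 5.9% |
| 200 | 20% | 8.7% |

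**Step 5: contamination (assumed shares).** If a share c of controls gains the full 1000 steps, the contrast is 1000 × (1 − c). Power is by normal approximation with 319 per arm.

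| Assumed c | Contrast | Power |
|---|---|---|
| 0% | 1000 | 80% |
| 5% | 950 | 76% |
| 10% | 900 | 71% |
| 20% | 800 | 61% |

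The documents supply neither b nor c. The 1000 steps in the plan is a difference between city means, not a gain per exposed person, so Step 5 only illustrates scale. Both tables use the planned evaluable size and take no credit for the gain in power expected from baseline adjustment.

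**The case against.** The strongest reply is that the differential part is small. Both arms sit through the same long interview on activity, intention, self-efficacy and tracking devices, and both then wear a pedometer and write down their steps. Only the increment from a few campaign items differs, and it falls on people whose districts have had a year of that campaign. No text shows that the prompt changes walking, and with an assumed 100 steps the rejection rate barely moves. All of this stands: the prompt is a risk created by the stated order, not a demonstrated bias.

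On contamination, the intervention is aimed at residents of the chosen Duesseldorf districts, with signage and workplace projects located there. City of work at T0 allows a rough check that excludes controls who work in Duesseldorf. That also stands, but it is a weak proxy: it says nothing about media or website contact, and it predates the campaign.

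Three stronger readings are tempting but not supported.

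- **That the attribution question cannot be answered because controls get no awareness items.** The Introduction asks how far "these differences be attributed to the adoption, implementation, and maintenance of the intervention in the intervention city compared with the control city". Process Evaluation measures those three components on organisations: the proportion implementing, an implementation score, and the intention to continue. Awareness items for Wuppertal residents would not supply them.
- **That the comparison of aware with unaware people is faulty for lack of adjustment for baseline activity.** An article commonly leaves covariate detail of this kind to the full plan.
- **That the campaign is open to everyone, or that cross-city working is expected.** The article states neither. It shows only channels that could reach controls, and an item on city of work.

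**Conclusion.** The point holds as a low-cost improvement to a stated procedure. The article places campaign-specific items before the primary outcome in one arm only, and it collects no campaign awareness or use in the other. The first could bias the contrast towards the intervention. The second leaves contamination, which would bias it towards zero, and false-positive recall without a direct estimate.

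The size of each is unknown, and since they act in opposite directions the net effect cannot be signed. A reader might infer that the primary result is biased by a known number of steps. The documents do not support that: 100 to 200 steps for the prompt and 5% to 20% for exposed controls are assumptions, chosen to show when the matter would begin to count against a 1000-step target. The conclusion rests on reading the Table 2 footnote, the placement of the items in the follow-up interview, and the order of interview and wear week as they stand.

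**What to change.** 1. Ask the same awareness and use items in both cities.
2. Ask them after the pedometer week, for example on a sheet returned with the diary and device, or in a short call, so that nothing campaign-specific comes before the primary outcome in either arm.
3. Report awareness and use in Wuppertal as contamination and false recall. A single awareness proportion mixes the two; items on use of specific components are closer to true exposure.
4. Use the Wuppertal answers in a sensitivity analysis of the primary contrast, for example without controls who report use. Keep it as a sensitivity analysis, since it selects on answers given after baseline.

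Cost: a few minutes per control participant and a change in the order of items. A mailed sheet would also replace interviewer-collected answers with self-completed ones, and some would not come back, which would weaken the reach estimate somewhat; a short call limits that loss at the price of staff time. On the article's timetable, publication in September 2022 preceded the start of follow-up in May 2023, so the change fitted before T1.
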